# Protocol for a randomized clinical trial comparing the efficacy of Structured Diet (SD) and Regular Therapy (RT) for adolescents with malnutrition having Autism Spectrum Disorder (ASD)

**DOI:** 10.1371/journal.pone.0292326

**Published:** 2023-11-29

## Abstract

**Background:**

Autism spectrum disorders (ASD) have a lifelong impact on behavior, communication, cognitive function, education, physical functioning, and personal, or social life. Separate studies suggest, Therapeutic and dietary interventions are effective to some extent in managing these issues. No study integrated the nutrition and therapeutic approaches and examined the outcome on disease severity, overall health, and behavioral status in ASD. The proposed study is designed to evaluate the combined effect of regular therapy (RT) and structured diet (SD) compared to the usual diet (UD) for Adolescents with ASD.

**Methods:**

The proposed study will be a randomized clinical trial (RCT) with the assessor, therapist, and participants blinded to group allocation. Seventy ASD children with malnutrition will be enrolled in two different facilities of the Centre for the Rehabilitation of the Paralysed (CRP) between January 2023 and June 2023. Participants will be enrolled through a hospital-based randomization process from a population-based screening dataset, and with a concealed group allocation to either RT+ SD or RT+ UD group with a 1:1 ratio. The outcome measures are the Childhood Autism Rating Scale as per DSM‐5 to determine the severity of ASD, Mid-upper arm circumference (MUAC), and BMI for nutritional status, and Gilliam Autism Rating Scale (GARS-2) to assess the behavioral status. Post-test will be performed after 12 weeks of intervention, and Follow-up will be taken after 6 months of post-test.

**Perspectives:**

The result of the study will contribute to the provision of a comprehensive approach to malnourished Adolescents with ASD, and manage the issues related to the severity of ASD, stereotypical behavior, and anticipated health hazards.

**Clinical trial identifier:**

CTRI/2022/11/047653.

## Introduction

Autism is one of the leading neuro-developmental disorders in the global context that interferes with social communication and basic conduct [1]. Although it can be diagnosed at any age, the manifestations of ASD are often delivered throughout the first two years of life [1, 2]. Autism Spectrum Disorder (ASD) affects people of all ethnic, racial, and socioeconomic backgrounds [1–3]. Children with ASD experience a variety of social problems, and repetitive or restricting behavior that is commonly observed during interaction, language, and communication [4, 5]. In Bangladesh, the prevalence of ASD has been steadily growing [6]. However, there is no epidemiological evidence of the overall number of autism cases in Bangladesh. Data from the Bangabandhu Sheikh Mujib Medical University’s Center for Neurodevelopment and Autism in Children suggest that 7.5 per 10,000 adolescents [7]. The study suggests, a larger proportion of children with ASD in urban areas seek treatment from a tertiary facility named the Institute of Pediatric Neuro Disorders and Autism (IPNA). National-level research on 7200 people conducted in Bangladesh in 2013 discovered a prevalence of ASD of 1.5 in 1000 children [8]. The rate was higher in Dhaka City (30 out of 10,000 children), compared to rural areas (7 out of 10,000 children) [7, 8].

Children’s growth, development, and nutritional condition are valuable indicators for determining children’s health [9]. Children with ASD may experience issues related to inadequate nutrition, such as limited eating behavior, appetite suppression, or metabolic issues leading to inadequate growth [10]. A study in Bangladesh found children with ASD had significantly lower height and weight, wider triceps and supra-iliac skin fold, and were underweight in comparison to non-ASD children [11]. The reason might be, they are often neglected at the dietary level due to the lack of awareness and non-adherence to evidence-based interventions. There is no structured dietary protocol for children and adolescents with ASD in Bangladesh. Global researchers from different countries found a positive effect of structured dietary protocols for children with ASD [12]. Improper diet can lead to gastrointestinal manifestations including inflammatory bowel disease, food sensitivity and allergies, infections, and illnesses associated with biological and viral infections [13].

There have been several systematic reviews and meta-analyses [14–16] conducted on the nutrition of ASD children. There are different opinions on dietary interventions for ASD in Adolescents [12, 17, 18]. It is assumed that gluten-free and casein-free diets can minimize the symptoms of ASD, but there are controversial theories about the effectiveness of the gluten-free and casein-free (GFCF) diet [17]. According to certain studies, the GFCF diet can assist with symptoms such as stereotyped attitude, cognitive and social function, attention, interaction, and mood [18]. Many explanations have been proposed to explain how the GFCF diet improves the features of autism. Of all of these, the opioid excess hypothesis is the most widely accepted. Gluten and casein both affect the central nervous system via the leaky gut, but opioids escape via inflamed and thinning stomach in children with ASD [12].

Therapeutic interventions are multidisciplinary approaches [19] that, composed of balance [20], gait training [21], Therapeutic horse riding [22], motor training [23], strength training [24], aerobic exercise [25], and executive functional tasks [26]. It is hypothesized that structured dietary intervention adjunct with regular treatment approaches may have a greater benefit in children with ASD but no such research in Bangladesh has been held yet. It is important to determine the combined outcome of a structured diet (SD) and regular therapy (RT) for improving nutritional status and behavioral indices in the child and adolescents with malnutrition having Autism in Bangladesh.

The study objectives are to (1) determine the socio-demographics and anthropometric measures related to malnutrition for ASD in Bangladesh, (2) to elicit the within-group difference between structured diet (SD) with regular therapy (RT) or usual diet (UD) with regular therapy (RT) therapy on nutritional status and behavioral indices in post-test (3months) and follow-up (6months) compared to baseline, and (3) to find out the effectiveness among groups (SD with RT versus UD with RT) and observations (pretest to post-treatment, pretest to follow up, and post-test to follow up) comparison in the improvement of nutritional status and behavioral indices.

## Method

### Study design

The study will be a randomized clinical trial (RCT) with the assessor, therapist, and participants blinded to group allocation. ASD adolescents having malnutrition will be enrolled in two different facilities of the Centre for the Rehabilitation of the Paralysed (CRP) from January 2023 to June 2023. Participants will be enrolled through a screening process through a population-based cross-sectional household survey. Population-to-sample frame determination will be proceeded by stratified random sampling, sample enrollment in the trial will be performed by a hospital-based random sampling process and group allocation will be performed using concealed allocation. Both groups will have a similar number of participants (1:1).

To ensure the quality of the interventional study, we will follow Standard Protocol Items: Interventional Trials 2013 (SPIRIT) criteria for this experiment (Fig 1).

**Fig 1 pone.0292326.g001:**
[figure not shown]
Standard protocol items: Interventional trials 2013 (SPIRIT).

### Sample size

Sample size calculation has been performed through the software ClinCalc [S1 File] estimating the key outcome as the score of the Gilliam Autism Rating Scale (GARS 2) second edition [23, 30]. Sample size has been calculated [27] as the anticipated minimal clinically important differences (MCID) of GARS-2 [23] were estimated as 4.7±1.7 (0–10 Hiva scale converted from 0–126 GARS 2 score) with a baseline of 25% minimal clinical improvement, enrolment ratio 1:1, 80% power, and with the alpha value 0.05, the total sample stands as of 66. For safety we will enroll 70 ASD adolescents with a number of 35 participants in each group.

### Recruitment and randomization

The researcher will perform a sample frame to pool the samples for the interventional design. The sample frame will be taken from the dataset of the list of maltreated ASD Adolescents of Bangladesh screened by an early population-based household survey. From the sample frame, Participants living in Dhaka will be contacted one by one and will be invited to take part in this trial, thus hospital based-randomization will be ensured. After the pooled sample estimation, concealed allocation to groups will be performed using the “rand” function in Microsoft Excel 2010. Both groups will be treated in two different centers of an organization to ensure an equal level of care is being provided and prevention of cross-contamination of data. In the group allocation process, block randomization will be employed to ensure the balanced recruitment for two groups.

### Study procedure

After the trial registration is obtained, researchers will start the phone call procedure to estimate the willing participants. As the primary screening of cases of “ASD with malnutrition” performed in the population-based survey, the parents will be directly contacted for participating in the trial. From the computer-based random serial, the first 70 ASD will be pooled for enrollment in the study. On the first day, an assessor blinded to group allocation will further screen and take a pre-test assessment. Then the participant will be treated in a multi-disciplinary approach with the consultation of a nutritionist, physiotherapist (PT), Occupational therapist (OT), and speech and language therapist (SLT). Both structured dietary treatment and regular therapy will be provided as three 45 minutes sessions per week for a total of 12 weeks. After 12 weeks, the post-test data will be obtained by the assessor. There will be a follow-up evaluation after 6 months of post-test. There will be a separate assessor for each of the treatment set-ups. The Consolidated Standards of Reporting Trials (CONSORT) manual will be followed when conducting the study. Fig 2 provides a summary of the study’s methodology.

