### Eligibility criteria

Participants will be recruited if (1) aged between 13 to 18 years, (2) diagnosed as ASD children based on DSM-V criteria [28], (3) malnutrition according to Body Mass Index (BMI) [29], (4) not taking any diet advice or supplement, and (5) willing to participate. On the other hand, participants will be excluded if- (1) respondents provided consent but dropped out within the first week of enrollment, (2) allergy to any gluten-free, casein-free (GFCF), Soya free diet, (3) severe behavioral problems according to Gilliam Autism Rating Scale (GARS-2) [30].

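### The order of allocation and the day-one eligibility screen and pre-test is not fixed, and the text points to screening after allocation, where exclusions could differ by arm

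*Protocol article*

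**What the plan says.** All references are to the protocol article.

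- **Pooling.** Study procedure: "From the computer-based random serial, the first 70 ASD will be pooled for enrollment in the study".
- **Allocation.** Recruitment and randomization: "After the pooled sample estimation, concealed allocation to groups will be performed using the “rand” function in Microsoft Excel 2010".
- **Screen and pre-test.** Study procedure, directly after the pooling sentence: "On the first day, an assessor blinded to group allocation will further screen and take a pre-test assessment". The sentence after that opens "Then the participant will be treated in a multi-disciplinary approach with the consultation of a nutritionist". No allocation step stands between the two.
- **Assessors and centres.** Study procedure: "There will be a separate assessor for each of the treatment set-ups". Minimization of bias and blinding process also plans different assessors by centre. Study setting assigns one centre to control and the other to the experimental treatment.
- **Exclusions.** Eligibility criteria excludes "severe behavioral problems according to Gilliam Autism Rating Scale (GARS-2") without a cut-off, allergy related to the study diet, and anyone who consents but drops out in the first week.
- **Role of the GARS-2.** It is listed among the primary outcomes and is the basis of the sample size.
- **Analysis set.** Data analysis confines intention-to-treat to dropouts who had more than a month of treatment.

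**The concern.** Randomisation protects the comparison only for the people who are randomised and then analysed. If eligibility is decided after the arm is fixed, by a different person in each arm, the two sets can differ before any diet effect exists.

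The GARS-2 exclusion is the sensitive one. It acts on the scale that is later compared between arms, and with no cut-off in the article it rests on each assessor's judgement. The assessor is described as blinded, but that is weak protection where each assessor works at a centre that treats one arm only.

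The survey that supplies the names is described as having screened for autism with malnutrition. It is not said to have applied the GARS-2 exclusion, so that exclusion plausibly falls to the day-one screen.

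The first-week dropout rule works the same way. It removes people after enrolment, possibly for reasons linked to the assigned regimen, and the intention-to-treat rule does not reach them.

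**Working it through.** **1. Order of events**

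| Step | Section | What is fixed |
|---|---|---|
| First 70 pooled | Study procedure | Before the day-one screen |
| Allocation | Recruitment and randomization | After pooling; not placed relative to the screen |
| Further screen and pre-test | Study procedure | Day one, before treatment |
| Treatment | Study procedure | Next step; no allocation in between |

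Two orders fit: pool, allocate, screen, treat; or pool, screen, allocate, treat. The second needs a step that Study procedure does not contain. The first also fits having one assessor per single-arm centre, since the centre is known only once the arm is. The first is therefore the more natural reading, but it is an inference.

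**2. The plan's own sample size**

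Inputs from Sample size: mean 4.7, SD 1.7, 25% improvement, 80% power, alpha 0.05 (two-sided assumed).

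- Difference: 0.25 × 4.7 = 1.175.
- n per arm = 2 × [1.7 × (1.960 + 0.842) / 1.175]² = 32.86, rounded up to 33, total 66. This matches the stated 66.
- Margin: 70 − 66 = 4.

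Power by normal approximation, Φ(1.175 / (1.7 × √(2/n)) − 1.96), is 82.4% at 35 per arm, 80.2% at 33, 79.0% at 32 and 76.3% at 30. The point does not rest on a sample-size error, and a few exclusions cost little power.

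**3. Illustration of differential exclusion**

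Assumptions not in the documents: normal scores with SD 1.7, one centre removes its highest scorers, and the other removes none. If a fraction x is cut from the top, the mean falls by SD × φ(z) / (1 − x), where z is the upper x point of the normal distribution.

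- x = 3/35: 0.171 SD; 0.171 × 1.7 = 0.29 points at baseline.
- x = 5/35: 0.263 SD; 0.263 × 1.7 = 0.45 points at baseline.

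The post-test mean shifts by this amount times the baseline–outcome correlation ρ, which the article does not give:

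| Assumed ρ | 3 of 35 removed | 5 of 35 removed |
|---|---|---|
| 0.5 | 0.15 (12% of 1.175) | 0.22 (19%) |
| 0.7 | 0.20 (17%) | 0.31 (27%) |
| 0.9 | 0.26 (22%) | 0.40 (34%) |

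Over a wider grid, with 5% to 20% removed at one centre and ρ from 0.5 to 0.9, the post-test bias runs from 0.09 to 0.54 points. Two-sided type I error then runs from about 6% to 24%. If both assessors apply the same criterion, the expected shift is zero.

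**The case against.** The strongest reply is that no sentence places allocation before day one. The term for the pooling stage is not defined and might include the further screen. An assessor described as blinded is compatible with a screen done before the assignment is revealed. The place of the screen is not given, and the sentence on separate assessors follows those on the post-test and follow-up. The flow chart (Fig 2) is not shown here and may settle the order. All of this stands, so the point is that the order is not fixed, with the text leaning one way.

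A reader might infer more than the documents support:

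- **That the protocol states post-allocation screening.** It does not, for the reasons above.
- **That the allergy exclusion is judged after allocation.** Safety measures and managing adverse effects has parents asked about food allergies before the start, which could be at any earlier contact. Nothing here depends on that exclusion.
- **That 25% or 38% of the planned effect is at risk.** Those are the baseline shifts divided by 1.175 (0.29/1.175 and 0.45/1.175). They set a worst-case baseline shift against an outcome difference; the post-test shift is smaller in proportion to ρ.
- **That the pre-test is spoiled as a covariate.** Data analysis names no covariate adjustment.
- **That losing more than 4 participants breaks the trial.** Power at 32 per arm is 79.0% against 80.2% at 33.

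The reply does not reach the first-week dropout rule, which is post-enrolment by its own terms.

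**Conclusion.** The point holds in limited form. The order of allocation and day-one screening is left open, and the text as written points to screening after allocation at a centre that is one arm with its own assessor. Exclusions on the GARS-2 could then be post-randomisation and differ by arm. First-week dropouts are removed after enrolment and not restored.

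Differential exclusion is a risk, not a documented event, and its size is unknown. The figure of 0.15 to 0.22 points at post-test rests on normal scores, SD 1.7, an assumed correlation of 0.5, and exclusions of 3 to 5 of 35 at one centre only. Its direction depends on which centre excludes more. The change is worth making because it is cheap and removes the risk whatever its size.

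**What to change.** For remaining enrolment:

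1. Complete consent, full eligibility screening and the pre-test (GARS-2, MUAC, BMI) before the person who randomises, who is already independent of the research, releases the assignment.
2. State one GARS-2 exclusion criterion in advance and apply it identically to everyone screened. Its value is for the investigators to set.
3. Continue down the random serial until 70 eligible participants are randomised, so that screening failures do not come out of the 70.
4. Analyse all randomised participants as allocated, including first-week dropouts, and remove first-week dropout from the exclusions.
5. Study status says recruitment has started. Report the order actually used for those already enrolled, with any exclusions by arm and reason.

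The cost is an amendment to the visit order and some extra families screened from the existing list. If the flow chart or full protocol already places screening before allocation, the text need only say so, and items 2, 4 and 5 remain.

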**Fig 2 pone.0292326.g002:**
[figure not shown]
CONSORT flow chart of the proposed trial.

### Study setting

Both of the groups will receive treatment from two different centers of the Centre for the Rehabilitation of the Paralysed (CRP), the largest rehabilitation facility in Bangladesh. Specification of centers for therapy group allocation will not disclose, to ensure the physiotherapists and the patients are blinded to group allocation. Two study centers of an organization (one for control and one for experimental) were selected because of the availability of specialist multi-disciplinary team of physiotherapist, occupational therapist, speech and language therapist, child psychologist, educational psychologist, nutritionist and special educators were available altogether in that specialized organization.

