### Minimization of bias and blinding process

Assessors, patients, and therapists will be blinded to group allocation in this study. As this will be a multi-center trial of an organization, researchers plan to different assessors for each center. Randomization will be done by a person who is not involved in this research. The treatment providers will be blinded to the groups, but they will be aware of the treatment of their group, also participants will not be aware of the intervention of another group. The execution of the study will not involve the research team, and a separate assessor, treatment provider, monitoring team, and trial manager will be employed to guarantee trial coordination.

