### Data analysis

According to the nature of the data, SPSS version 23 for Windows will be used for analysis. The distribution of data will be performed using normality indicators and normality tests such as the Kolmogorov-Smirnov test, and the Shapiro-Wilk test. Descriptive analysis will be performed by mean and standard deviation for the continuous data, and frequency and percentage categorical data. The baseline compatibility, between-group post-test, and follow-up variations among the groups will be assessed using MANOVA or the Multivariate Kruskal-Wallis (MKW) test, depending on the nature of the data. Repeated measure or Friedman’s ANOVA Three measures will be analyzed within-group using an ANOVA, and additional post-hoc analyses will be performed using paired sample t-tests or Wilcoxon tests. We will perform the intention to treat the analysis process for the drop-out of cases taking more than one month of interventions. In the case of a post hoc Bonferroni adjustment, the level of significance P < .05 will be converted to P < .0125.

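### Each arm is treated and assessed at its own single centre, so the structured-diet effect cannot be separated from centre or assessor differences by any analysis

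*Protocol article*

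**What the plan says.** Under Study setting the protocol article states "Two study centers of an organization (one for control and one for experimental) were selected". Recruitment and randomization gives the reason: "Both groups will be treated in two different centers of an organization to ensure an equal level of care is being provided". The same sentence adds a second reason, preventing cross-contamination between groups.

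Assessment follows the same split. Study procedure says "There will be a separate assessor for each of the treatment set-ups", and the section on minimization of bias says "researchers plan to different assessors for each center".

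Allocation itself is individual: "block randomization will be employed to ensure the balanced recruitment for two groups". Stratification by centre is not mentioned. The between-group comparisons "will be assessed using MANOVA or the Multivariate Kruskal-Wallis (MKW) test, depending on the nature of the data"; no centre term is mentioned there. No section places both arms at either centre.

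**The concern.** The third study objective compares structured diet plus regular therapy with usual diet plus regular therapy. That contrast isolates diet only if regular therapy and outcome measurement are the same in both arms. Randomisation balances who enters each arm. It does not balance what happens after allocation, and here everything that belongs to a site (therapy team, local delivery, assessor) comes with the arm.

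The protocol leaves room for such differences. Under Intervention, treatment dosage depends on age, symptoms and severity, and speech and language therapy is based on the individual's symptoms. A primary outcome, the GARS-2, is a rating scale scored by a different assessor in each arm.

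A positive result could be partly or wholly a centre or rater difference. A null result could be a diet benefit offset by one. The data could not show which.

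**Working it through.** **Inputs from the protocol article**

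- Mean and standard deviation on the 0-10 scale: "were estimated as 4.7±1.7" (Sample size). With 25% improvement, the planned difference is 0.25 × 4.7 = 1.175.
- 80% power, alpha 0.05, 1:1 allocation, 66 in total, 70 enrolled. That is 35 per group, hence 35 per centre. Sidedness is not stated.

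**Assumed, because the documents give no figure:** the size of the centre difference, or the intra-centre correlation ρ. The illustrations use a single-outcome two-sample test under the normal approximation.

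**Step 1. The plan's own figure.** n per arm = 2 × (1.960 + 0.842)² × 1.7² / 1.175² = 32.9, so 33 per arm and 66 in total. The stated total reproduces with a two-sided test (a one-sided test would give 52). The calculation allows for no centre effect.

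**Step 2. Can the diet effect be identified?** Write outcome = μ + τ·arm + γ·centre + error.

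- As designed, arm = centre for every participant, so the difference in means estimates τ + γ. The design matrix [intercept, arm, centre] for 70 participants has 3 columns but rank 2.
- Adding a baseline covariate gives 4 columns and rank 3. The problem remains.
- A random centre effect or a cluster-robust variance has one centre per arm, hence 0 degrees of freedom for between-centre variance.
- Change from baseline removes a stable level difference between sites or raters. It keeps any centre-specific improvement and any rater drift.
- If both arms were randomised within each centre, the rank would be 3 of 3 and both effects would be estimable.

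**Step 3. Illustration with a fixed centre difference γ and no diet effect.** SE = 1.7 × √(2/35) = 0.406. P(significant) = Φ(γ/SE − 1.96) + Φ(−γ/SE − 1.96).

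| True centre difference (0-10 scale) | P(significant) |
|---|---|
| 0.25 | 9.4% |
| 0.5 | 23.4% |
| 0.75 | 45.5% |
| 1.0 | 69.2% |
| 1.175 | 82.4% |

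**Step 4. Illustration averaged over hypothetical pairs of centres.** With total standard deviation σ, the true variance of the difference is 2σ²[ρ + (1 − ρ)/35]. The test sees only the within-centre part, 2σ²(1 − ρ)/35. The ratio is k² = 1 + 35ρ/(1 − ρ), and the actual error rate is 2[1 − Φ(1.96/k)].

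| Assumed ρ | k | Actual error of a nominal 5% test |
|---|---|---|
| 0.01 | 1.16 | 9.2% |
| 0.02 | 1.31 | 13.4% |
| 0.05 | 1.69 | 24.5% |
| 0.10 | 2.21 | 37.5% |

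At ρ = 0.05 the centre difference has standard deviation 1.7 × √(2 × 0.05) = 0.54 points, or 46% of the planned 1.175.

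**Step 5. Price of a centre term.** With all 70 randomised within centre, t-test power for 1.175 is 81.3% with a centre term (67 degrees of freedom) and 81.3% without (68).

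**The case against.** Both sites belong to one organisation, work to one protocol and offer the same listed therapies. The control arm receives regular therapy as described for the experimental arm. Separating the arms also has a legitimate purpose: families given dietary advice may share it, and preventing cross-contamination is a stated reason. The blinding scheme rests on the separation too, because Study setting withholds which centre serves which group.

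This has weight. One organisation may make the sites more alike, and contamination is a real risk in a dietary-advice trial. But similarity is an assumption that this design cannot test, and preventing contamination does not remove the aliasing. One sentence in Study setting could be read as placing both groups at both centres. The explicit one-centre-per-arm statement and the contamination rationale rule that reading out.

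Several stronger readings are tempting but go beyond the text:

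- A reader might infer that care does differ between the sites, or that separation makes it unequal. The documents report no difference in facilities or practice; only the separate assessors are stated. What they support is that equality is neither ensured nor verifiable.
- A reader might infer that each site's staff decide what therapy contains. The sentence under Progression of interventions leaves progression, not content, to the professionals. The room for variation comes from the tailored dosage and symptom-based speech therapy.
- A reader might infer that block randomisation is offered as a cure for the centre problem. The protocol claims only balanced group numbers for it, and that is no error.

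**Conclusion.** The point stands as a structural one. Arm, centre and assessor are completely aliased, and the effect of the structured diet cannot be estimated apart from the other two, whatever the analysis plan says. The claim that separate centres ensure an equal level of care describes a property that the design does not have.

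This conclusion rests on the text alone and not on any assumed variance. The error rates are illustrations. For these two particular centres the problem is a fixed bias of unknown sign and size, possibly small. The 9.2% to 37.5% range is an average over hypothetical centre pairs at assumed correlations of 0.01 to 0.10, not an estimate for this trial. A reader might infer that the trial's result will be wrong. The documents support only that its attribution to diet cannot be checked from the data. The sample size arithmetic is correct and is not in question.

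**What to change.** **For all participants not yet allocated:** randomise 1:1 in permuted blocks stratified by centre, so that both arms are treated at both centres. Have each assessor rate both arms, and include centre as a factor in the between-group analysis.

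**For participants already allocated under one arm per centre:** analyse them as a separate stratum and state that it gives no unconfounded estimate of the diet effect. The 81.3% power applies only if all 70 are randomised within centre; with fewer it is lower.

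**Costs:** a protocol amendment and a stratified allocation list. Some sharing of diet advice within a site becomes possible; it would mainly dilute the effect, whereas the aliasing can bias in either direction. The blinding that rests on undisclosed centres becomes weaker. Study setting describes the specialist team as available in the organisation, so the presence of a nutritionist at each site must be confirmed.

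**If allocation is complete or the design is kept:** this may be the only option, since enrolment was planned for January to June 2023, recruitment is reported as started, and the article is dated November 2023. Then remove the claim that separate centres ensure equal care. State in the protocol and the final report that the between-group result is the joint effect of diet, centre and assessor, and qualify any attribution to the structured diet accordingly. This costs only wording.
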